## Goal

The goal of this research is to guide malaria elimination programs in Zambia on how to best utilize reactive responses to accelerate toward zero transmission and to establish, document and sustain malaria free zones.

## Aims

The study’s goal will be addressed through the following specific aims:

**Primary Aim**: Compare the effectiveness of RFDA using DHAP with RFTAT using AL in achieving zero seropositivity in children under fifteen.

**Secondary Aim 1**: Compare the effectiveness of RFDA using DHAP with RFTAT using AL in reducing RDT confirmed malaria incidence through passive case detection at health facilities.

**Secondary Aim 2**: Compare the effectiveness of RFDA using DHAP with RFTAT using AL in reducing the prevalence of malaria and preventing re-infection in individuals receiving reactive responses.

**Secondary Aim 3**: Compare the cost-effectiveness of RFDA using DHAP with RFTAT using AL in reducing the burden of malaria in the community.

**Secondary Aim 4**: Measure the proportion of *P. falciparum* infections likely attributable to importation and local transmission using parasite genotyping as well as defining genotypes spatial distribution.

**Secondary Aim 5**: Assess the utility of using serology to measure short-term changes in malaria transmission and evaluate malaria elimination programs.

**Secondary Aim 6**: Assess the feasibility of using remotely sensed malaria risk maps to identify areas with higher potential for local malaria transmission.

**Secondary Aim 7:** Assess the utility of a HS RDT in identifying additional standard RDT sub-patent infections in the RFDA arm.

# Research Plan

## Study Design

The study design will be a cluster randomized trial comparing an enhanced strategy for malaria elimination (RFDA with DHAP) with the current strategy (RFTAT with AL). Impact evaluation will consist of: 1) community-based, cross-sectional measurement of malaria seropositivity in children aged ≥ 1 month and < 15 years through a random sample survey at the end (two years) of the intervention period; 2) longitudinal follow-up of a subset of individuals participating in reactive responses by a research team; and 3) detection of incident malaria cases and total outpatient attendance at health centers and health posts.

A total of sixteen health centers will be targeted in this RCT (Table 1). The proposed areas were selected from the 11 districts within Southern Province, Zambia that have successfully implemented RFTAT surveillance with the following criteria: a mean monthly incident malaria case load of < 25 and a mean test positivity during ongoing RFTAT of at least 5%. Where multiple health centers fulfilled the inclusion criteria, preference was given to those that are geographically close to one another (minimum 5km buffer to reduce contamination) and are accessible all year round. Selected health centres will be randomized to either control or intervention arms, with 8 health centers per arm (Figure 3).

| Organisation Unit | Confirmed Cases of Malaria (Sep ’13 – Aug ’14) | | | | Positivity Rate (%) during RFTAT |
| --- | --- | --- | --- | --- | --- |
|  | Clinic | Community | Total | Average cases per month |  |
| Chisekesi Rural Health Centre | 176 | 77 | 253 | 21 | 9.4 |
| Habulile Rural Health Centre | 133 | 109 | 242 | 20 | 9.3 |
| Katombora Health Post | 123 | 78 | 201 | 17 | 12 |
| Kazungula Health Post | 71 | 20 | 91 | 8 | 7.9 |
| Keemba Rural Health Centre | 58 | 89 | 147 | 12 | 6.8 |
| Mayoba Rural Health Centre | 46 | 37 | 83 | 7 | 9.4 |
| Moonde Rural Health Clinic | 0 | 214 | 214 | 18 | 8.3 |
| Mubanga Rural Health Centre | 77 | 139 | 216 | 18 | 5.3 |
| Mukwela Rural Health Centre | 86 | 157 | 243 | 20 | 7.8 |
| Munkolo Rural Health Centre | 42 | 76 | 118 | 10 | 6.9 |
| Musokotwane Health Post | 38 | 53 | 91 | 8 | 8.2 |
| Muzya Rural Health Centre | 40 | 83 | 123 | 10 | 9.9 |
| Nadezwe Rural Health Centre | 58 | 107 | 165 | 14 | 11.2 |
| Namwianga Urban Health Centre | 56 | 140 | 196 | 16 | 5.2 |
| Ngwezi Rural Health Centre | 11 | 169 | 180 | 15 | 8.3 |
| Pangwe Rural Health Centre | 21 | 127 | 148 | 12 | 19.2 |
| Siachitema Rural Health Centre | 14 | 119 | 133 | 11 | 7.4 |
| Simooya Rural Health Centre | 142 | 40 | 182 | 15 | 8.7 |
| Zambia National Service Rural Health Centre | 78 | 40 | 118 | 10 | 10.7 |
| ZCA Rural Health Centre | 215 | 47 | 262 | 22 | 8.3 |

Table 1 – Proposed selected health centre catchment areas along with data from these facilities for the last year.

**Control Arm** - PCD at health centers and health posts, with RFTAT in response to RDT confirmed incident malaria cases as currently outlined in the Step D protocol (Appendix 1). RFTAT consists of screening all individuals within 140 meters of an incident malaria case using a RDT and treating those testing positive with AL.

**Intervention Arm** - PCD at health centers and health posts, with RFDA in response to RDT confirmed incident malaria cases. RFDA consists of treating all individuals within 140 meters of an incident malaria case with DHAP.

[figure not shown]

Figure 3 - Schematic showing control and intervention arms proposed at the health center catchment level. PCD, passive case detection; RFTAT, reactive focal test and treat; RFDA, reactive focal drug administration; AL, artemether-lumefantrine; DHAP, dihydroartemisinin-piperaquine.

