# Health Facility hierarchy in Zambia

To avoid confusion, it is necessary to clarify terminology around health facilities. For the purposes of this document, the term rural health clinic (HC / RHC) will refer to all government run facilities that act as the primary location for health care service delivery and which are manned by professional health workers. In contrast, a rural health post (HP / RHP) is a satellite facility attached to an individual health centre that aims to expand health care access for a few key interventions, namely malaria testing and treatment. HP’s are predominantly manned by volunteer community health workers. The term health facility will refer to both HC’s and HP’s.

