# Project summary

| **Primary Aim** | Compare the effectiveness of RFDA using DHAP with RFTAT using AL in achieving zero seropositivity in children under fifteen |
| --- | --- |
| **Secondary Aims** | 1. Compare the effectiveness of RFDA using DHAP with RFTAT using AL in reducing RDT confirmed malaria incidence through passive case detection at health facilities. 2. Compare the effectiveness of RFDA using DHAP with RFTAT using AL in reducing the prevalence of malaria and preventing re-infection in individuals receiving reactive responses. 3. Compare the cost-effectiveness of RFDA using DHAP with RFTAT using AL in reducing the burden of malaria in the community. 4. Measure the proportion of *P. falciparum* infections likely attributable to importation and local transmission using parasite genotyping as well as defining genotype spatial distribution. 5. Assess the utility of using serology to measure short term changes in malaria transmission and evaluate malaria elimination programs 6. Assess the feasibility of using remotely sensed malaria risk maps to identify areas with higher potential for local malaria transmission. 7. Assess the utility of a HS RDT in identifying additional standard RDT sub-patent infections in the RFDA arm |
| **Study Site & Target Populations** | Population of ~130,000 people in ~30,000 households in 16 Health Center catchment areas in Southern Province. |
| **Study design** | Cluster randomized controlled trial will be used to evaluate the impact of RFDA intervention against current standard of care for the impact on seropositivity in children under fifteen years, passive surveillance for confirmed malaria case incidence, and elimination of transmission from hotspots |
| **Primary outcome measures for assessing program impact** | 1. Malaria seropositivity in children under fifteen after two-year intervention within health center catchment areas 2. Confirmed malaria incidence as measured through routine passive case detection at health centers and health posts throughout the selected health center catchment areas |

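### Table 1 offers 20 units, three named health posts, for 16 cluster places, and no restriction on allocation is stated beyond eight per arm although baseline malaria data are at hand

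*Protocol*

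**What the plan says.** The Study Design section sets the number of clusters and points to the table: "A total of sixteen health centers will be targeted in this RCT (Table 1"). It continues: "Selected health centres will be randomized to either control or intervention arms, with 8 health centers per arm". The Project summary agrees: "Population of ~130,000 people in ~30,000 households in 16 Health Center catchment areas in Southern Province". Eight per arm recurs under the Primary Aim, Secondary Aim 1 and Survey Sample Size.

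Table 1 is captioned "Proposed selected health centre catchment areas along with data from these facilities for the last year" and has 20 rows. Three of them are Katombora, Kazungula and Musokotwane Health Posts, and one is an urban health centre. The section on the health facility hierarchy says that "a rural health post (HP / RHP) is a satellite facility attached to an individual health centre".

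The selection criteria are fewer than 25 incident cases a month and at least 5% positivity during RFTAT. Where several centres qualified, nearby and accessible ones were preferred, with a 5 km minimum buffer mentioned in that clause. No stratification, matching or other constraint on the allocation is stated.

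The Primary Aim is assessed on seropositivity at endline. Its adjustment list covers environment, socio-economic status, housing, education, demographics, nets and spraying.

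**The concern.** Two matters have to be settled before anything is randomised, and a later analysis document cannot settle them.

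The first is what the clusters are. The text says 16 health centres and the cited table shows 20 units. Three of those carry a label that, by the Protocol's own definition, makes them part of another catchment. If such a post were randomised apart from its parent centre, one community could be served by two strategies, depending on where a patient presents.

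The second is how the clusters are divided. With eight per arm, a simple draw can leave the arms at different starting levels of malaria. Seropositivity has no baseline measurement in the design, so the difference-in-differences approach named in the Project summary cannot remove such a difference from the primary outcome. The planned covariates do not include prior caseload or positivity. The data needed to prevent the imbalance are already in Table 1.

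**Working it through.** **1. The Protocol's own cluster count.** 2 arms × 8 = 16 clusters, and 16 × 500 children = 8,000, as in the Project summary. The Hayes-Bennett formula supports eight per arm: c = 1 + (1.960 + 0.842)² × [p0(1−p0)/m + p1(1−p1)/m + k²(p0² + p1²)] / (p0 − p1)². The inputs are p0 = 0.05, k = 0.5 and m = 500. The bold 61.7% in Table 3 gives p1 = 0.05 × 0.383 = 0.01915. The bracket is 0.0000950 + 0.0000376 + 0.0007167 = 0.0008493, and (p0 − p1)² = 0.0009517. Then c = 1 + 7.849 × 0.0008493 / 0.0009517 = 8.0. (The 64.5% in the accompanying text is a separate matter.)

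**2. Table 1 against that count.** There are 20 rows: 3 health posts, 1 urban centre and 16 rural health centres or clinics. Every row total and monthly average checks. The highest monthly average is 22, below 25, and the lowest positivity is 5.2%, above 5%. The numeric criteria therefore remove no unit, and the remaining criteria are worded as preferences. Nothing in the Protocol leads from 20 to 16.

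**3. The three posts.** The Protocol names no parent centre for any of them. If a post and its parent were both among the 16 and were randomised separately by a simple 8:8 draw, they would fall in different arms with probability 8/15 = 53%. Whether that situation arises cannot be told from the document.

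**4. Spread of the baseline measures.** Over the 20 units, annual cases run from 83 to 262 (262/83 = 3.2-fold) and positivity from 5.2% to 19.2%.

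**5. Imbalance under a simple draw (illustration).** I took the 16 rural units, which have 2,827 cases in all (mean 176.7) and mean positivity 9.2%. I enumerated all C(16,8) = 12,870 splits and formed the ratio of the larger arm mean to the smaller.

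| Measure | Median ratio | Splits with ratio above 1.2 |
|---|---|---|
| Annual cases | 1.12 | 3,300 (25.6%) |
| RFTAT positivity | 1.16 | 4,314 (33.5%) |
| At least one of the two | – | 6,456 (50.2%) |

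The caseload ratio exceeds 1.5 in only 0.8% of splits.

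**6. Sensitivity to one unit.** Pangwe has positivity 19.2%; the next highest is 11.2%. With Pangwe set to the mean of the other 15 (8.5%), 3.5% of splits exceed 1.2 on positivity, down from 33.5%.

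**7. Room for restriction.** Requiring both ratios to be at most 1.1 leaves 1,606 of 12,870 splits (12.5%). No pair of units is always together or always apart in that set. Pairs share an arm in 19% to 83% of the acceptable splits, against 7/15 = 47% under a simple draw.

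**The case against.** Several stronger readings are tempting, and the Protocol does not support them.

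- **Sixteen units are drawn at random from 20.** No such draw is described. The table is headed as proposed, sites are selected first and randomised afterwards, and the 17 units that are not posts could fill every place.
- **Catchments will be split between arms.** This is a possibility, not a fact. The Primary Aim and Figure 3 place randomisation at the level of the whole health centre catchment, and both arms are described as covering health centres and health posts. A row named Health Post may be a facility that functions as a centre: all three report clinic as well as community cases, for example "Katombora Health Post | 123 | 78 | 201 | 17 | 12" (the first two figures are clinic and community). The 5 km separation at site selection also bears on contamination, although it sits in a preference clause.
- **Allocation is unrestricted.** The Protocol is silent beyond eight per arm; it does not say that no restriction applies.
- **The imbalance biases the trial.** Chance imbalance under randomisation is not bias, and the sample size already allows for between-cluster variation with k = 0.5.
- **The urban centre should be dropped.** It meets both criteria (16 cases a month, 5.2% positivity), and nothing in the Protocol excludes it.

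Three limits on the figures also stand. The positivity result rests largely on one unit. Table 1 gives raw case counts without catchment populations, so unequal counts need not mean unequal burden. The 20% threshold is a choice made for illustration.

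What the objection does not remove is that the 16 clusters are unnamed, that the Protocol's definition and its table disagree about the posts, and that known baseline information is given no stated role in the allocation or in the primary adjustment. For incidence, routine data from before the intervention could supply a baseline. For seropositivity, the primary outcome, the design has none.

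**Conclusion.** The point holds in a limited form. The mismatch between 16 and 20, and the status of the three posts, call for clarification. Whether any post could be separated from its parent depends on facts that the Protocol does not give.

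The allocation point carries more weight. If the draw is a simple 8:8 split of units like the 16 rural ones, there is about a one in four chance that mean caseload differs by more than 20% between arms. For positivity the chance is about one in three, falling to 3.5% without the outlying unit. About half of all splits exceed 20% on at least one measure.

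The consequence is lost precision and a result that is harder to defend, in a trial with eight clusters per arm and an endline-only primary outcome. It is not a biased comparison. These sizes assume the Table 1 data, those 16 units and no restriction on the draw. The simulation behind this review that took 16 from all 20 units gave a similar picture, with a ratio of 1.25 or more in 19% of draws for case totals and 18% for mean positivity.

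**What to change.** 1. Before randomisation, replace Table 1 with the final list of 16 catchments and state how they were chosen. The urban centre may stay. For each listed post that stays, either confirm that it is a catchment of its own or randomise it together with its parent centre as one cluster.
2. State a restricted allocation: either stratified, or one split drawn at random from the 8:8 splits in which the arm means of caseload and positivity agree within a preset margin. Caseload per head is preferable if catchment populations are available by then. The margin should leave many acceptable splits. For the 16 rural units, 10% on both measures leaves 1,606; the count has to be redone for the final list.
3. Add the same baseline measures to the covariates of the primary analysis.

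The cost is a corrected table, a short allocation programme and slightly more analysis work. No clusters are added. Two cluster-level covariates use two of the 16 − 2 = 14 between-cluster degrees of freedom. If allocation has already taken place, steps 1 and 3 still apply, and the method actually used should be reported.

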## Treatment regimes

### Artemether-lumefantrine (AL) – Control arm

Any individual testing positive for circulating *P. falciparum* antigen by RDT will receive treatment of age- and weight-appropriate doses of AL unless below 3 months in age or 5kg in weight, as per Zambia National Malaria Treatment Guidelines. Women of reproductive age (12-49 years) will be asked about their pregnancy status and if pregnant, the last time they felt the baby move. For women reporting that they are pregnant and have not felt the baby move (still in the first trimester) they will be referred to the nearest health center if testing positive. Pregnant women beyond the first trimester who test positive will be treated with AL according to Zambia National Malaria Treatment Guidelines. If a child with a weight less than 5kg or age less than or equal to 3 months tests positive for circulating malaria antigen they will be treated with sulfadoxine-pyrimethamine (SP), as per Zambia National Malaria Treatment Guidelines, or referred to the health center as appropriate. A summary of the decision tree that will be adhered to in this study is shown in Figure 4. A fixed dose of AL currently consists of combination tablets containing 20 mg of artemether and 120 mg of lumefantrine, given twice a day for 3 days. Patients will be encouraged to take AL with food to aid drug absorption.

[figure not shown]

Figure 4 - Decision tree for patient interactions during passive case detection at the health center / health post and RFTAT with AL in the community. mRDT, malaria RDT; WRA, Women of Reproductive Age; HC, Health Center; AL, Artemether-lumefantrine; SP, Sulphadoxine-pyrimethamine.

### Dihydroartemisinin - piperaquine (DHAP)

DHAP has been approved by the Zambian Ministry of Health as the second-line standard of care drug for the treatment of uncomplicated malaria in Zambia (AL is currently the first-line treatment). Overall, DHAP is safe, effective and well-tolerated by individuals

^30,31^. A recent study of intermittent preventive treatment of children in Uganda found that monthly administration of DHAP to children in primary school was both safe and effective

^32^, and previously in Thailand monthly administration of DHAP to adults was found to be both safe and effective

^33^. However in Zambia the administration of DHAP will be limited to twice yearly with at least two months in between doses, in accordance with the manufacturer’s instructions.

A fixed dose of DHAP currently consists of combination tablets containing 40 mg of dihydroartemisinin and 320 mg of piperaquine. A target dose of 4 mg/kg/day dihydroartemisinin and 18 mg/kg/day piperaquine once a day for 3 days will be given.

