#### Treatment notes

For this study, DHAP will be given in Eurartesim© tablets. While full product details are available from the manufacturers Sigma Tau (www.sigmatau.com), the following key issues are highlighted when administering DHAP, and summarised as a decision tree in Figure 5. DHAP is not recommended during the first trimester of pregnancy. Women of reproductive age (12-49) will be asked about their pregnancy status and if pregnant, the last time they felt the baby move. Any woman unsure of her pregnancy status will be offered a rapid pregnancy test, or referred to the nearest health facility. Women reporting that they are pregnant and have not felt the baby move (still in the first trimester), testing pregnant through the rapid pregnancy test or who are unsure of their pregnancy status will be tested with a malaria RDT and referred to the health center if testing positive. Pregnant women before the first trimester will not be treated with DHAP; pregnant women beyond the first trimester will be treated with DHAP. Additionally, DHAP should be administered with water no less than 3 hours after the last food intake, and no food should be taken within 3 hours after each dose. Any individual who does not wish to take, or cannot take DHAP, for whatever reason, will be offered the standard of care i.e. AL.

If a patient vomits within 30 minutes of taking DHAP, the whole dose will be re-administered. If a patient vomits within 30-60 minutes, half the dose will be re-administered. Re-dosing will not be attempted more than once. If the second dose is vomited, the patient will be referred to the nearest health centre. No more than two courses of DHAP will be given within a 12 month period, with a 2 month window between the two courses due to the long elimination half-life of piperaquine. Individuals identified during RFTAT responses who have been treated with DHAP in the previous 2 months, or twice within the previous year will be given AL.
[figure not shown]

Figure 5 - Decision tree for patient interactions during passive case detection at the health center/ health post and RFDA with DHAP in the community. mRDT, Malaria RDT; WRA, Women of Reproductive Age; HC, Health Center; DHAP, dihydroartemisinin-piperaquine. *due to previous dosing schedule.

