## Reactive responses

All reactive responses will aim to take place within 7 days following presentation of an RDT positive incident malaria case to a health center or health post within the study areas. Based on work showing the spatial distribution of malaria infections in Southern Province ([name] dissertation, unpublished), all individuals residing within 140 meters of the index case household will be included in the reactive response. In the control (RFTAT) arm, the current standard of care will be provided in which individuals will be tested for malaria using an RDT. Positive individuals will be offered treatment with AL or referred to a health center according to national treatment guidelines. In the intervention (RFDA) arm, all individuals residing within 140 meters of the index case household will be offered DHAP. Testing with an RDT will not be performed in the RFDA arm, with the exception of research team responses (see Section 2.4.1 on page 20).

[figure not shown]

Figure 6 - Schematic of activities before and during a CHW reactive response. HC, Health Center; HP, Health Post; AL, artemether-lumefantrine. Seated / standing figures indicate individuals who are symptomatic or healthy respectively. The colour of individuals represents whether they are infected with P. falciparum (Red) or uninfected (black).

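### The DHAP dose targets in Section 2.2.2 (4 and 18 mg/kg/day) cannot both be met with the 40/320 mg tablet, and Section 2.4's no-RDT rule omits people not given DHAP

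*Protocol*

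**What the plan says.** **Dose.** Section 2.2.2 describes DHAP as "combination tablets containing 40 mg of dihydroartemisinin and 320 mg of piperaquine". The next sentence fixes the regimen: "A target dose of 4 mg/kg/day dihydroartemisinin and 18 mg/kg/day piperaquine once a day for 3 days will be given". Section 2.2.2.1 (Treatment notes) names a single commercial product, Eurartesim, and says that "full product details are available from the manufacturers". The text available gives no weight bands, no acceptable range, no component that takes precedence, and no statement of whether the amounts are salt or base.

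**RDT use in the RFDA arm.** Section 2.4 states: "Testing with an RDT will not be performed in the RFDA arm, with the exception of research team responses". Section 2.2.2.1 says that women in early pregnancy, or of uncertain pregnancy status, "will be tested with a malaria RDT and referred to the health center if testing positive". Section 2.7 gives people who refuse DHAP the Zambian standard of care, which it describes as RFTAT with an RDT and AL.

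**Wording in Section 2.2.2.1.** Three further sentences matter here:
- "Any individual who does not wish to take, or cannot take DHAP, for whatever reason, will be offered the standard of care i.e. AL"
- "Individuals identified during RFTAT responses who have been treated with DHAP in the previous 2 months" (this begins the rule that sends such people to AL)
- "Pregnant women before the first trimester will not be treated with DHAP"

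**The concern.** The mg/kg sentence is the only weight-based DHAP dosing rule in the text available, and it governs the experimental drug. Its two halves conflict with the tablet described just before it. A reader who doses to one component misses the target for the other. Read as a target, the sentence therefore gives no standard against which a given dose can be judged correct.

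Piperaquine matters in both directions by the protocol's own account. Section 1.3 rests the prophylaxis rationale on its long half-life, and Section 2.2.2.1 limits repeat courses because of its slow elimination. The written rule for it should therefore be workable.

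The RDT conflict is smaller but real. Most reactive responses are carried out by a single CHW (Definitions of Key Terminology). Section 2.4 read alone tells that CHW not to test in the RFDA arm, while two other sections require a test in particular people who do not receive DHAP.

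**Working it through.** **Inputs, all from Section 2.2.2.** Tablet: 40 mg dihydroartemisinin (DHA) and 320 mg piperaquine (PQ). Targets: DHA 4 mg/kg/day and PQ 18 mg/kg/day.

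**1. Ratios.**
- Tablet PQ:DHA = 320/40 = 8.0
- Target PQ:DHA = 18/4 = 4.5
- Discrepancy = 8.0/4.5 = 1.78

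Whole, half or rounded tablets all keep the ratio at 8, so rounding and weight bands cannot close the gap. The stated pair of targets cannot be reproduced from the stated tablet.

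**2. What each reading delivers.**

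| Dose set by | DHA, mg/kg/day | PQ, mg/kg/day | Result against target |
| --- | --- | --- | --- |
| DHA at 4 | 4 | 4 × 8 = 32 | PQ 32/18 = 178% |
| PQ at 18 | 18/8 = 2.25 | 18 | DHA 2.25/4 = 56% |
| Equal ratio error on both | 3 | 3 × 8 = 24 | DHA 75%, PQ 133% |

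For the last row, let d be the DHA dose and set d/4 = 18/(8d). Then d² = 9 and d = 3. Even the best-balanced tablet count misses both targets, by 25% below and 33% above.

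**3. Tablets per day at weight w.** The DHA target needs 4w/40 tablets and the PQ target needs 18w/320.

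| Weight | DHA target | PQ target |
| --- | --- | --- |
| 20 kg | 2 | 1.125 |
| 40 kg | 4 | 2.25 |
| 60 kg | 6 | 3.375 |

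These counts restate the 1.78 ratio in tablets. They are arithmetic bounds, not expected exposures.

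**4. What would reconcile the figures.** A tablet meeting both targets would hold 40 × 18/4 = 180 mg of PQ per 40 mg of DHA. A salt/base difference would therefore work only if the basis of the 18 mg/kg figure were 180/320 = 56% of the basis of the 320 mg figure. The protocol states no such distinction.

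**5. RDT rules side by side.** Section 2.4 allows one exception to no testing in the RFDA arm, namely research team responses. Section 2.2.2.1 requires a test in early or uncertain pregnancy without limiting it to research responses. Section 2.7 describes RDT-based care for people who refuse DHAP, again without that limit. In a CHW-only response these instructions cannot all be followed as written.

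**The case against.** **Practice may follow the label.** Section 2.2.2.1 points to the manufacturer, and the RFDA decision tree (Figure 5) and CHW register (Appendix 18) are not in the text available. What field staff dose from is therefore unknown. This stands, and it limits the finding to the written instruction. It does not repair the sentence: the protocol says only that product details can be obtained, not that they override the stated dose.

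**The figures could be minimums.** Then 4 mg/kg of DHA with 32 mg/kg of PQ satisfies both. This is possible but weaker, because the sentence speaks of a target and PQ would run 78% above its figure.

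**The no-RDT sentence could be a general rule for people who receive DHAP.** On that reading the pregnancy and refusal rules are specific exceptions. This is a reasonable reading, but Section 2.4 lists its exception explicitly and omits these people. A short edit removes the doubt.

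**The wording slips are largely settled elsewhere.** This stands. Sections 2.4.1, 2.7 and 3.1 make the fallback RDT first. The same notes say that DHAP is not recommended during the first trimester. Figure 5 may cover recent DHAP, since its caption mentions the previous dosing schedule. These points are editorial only.

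**Two stronger readings are not supported.** A reader might infer that participants would be under- or overdosed, but nothing shown establishes what dose staff would give. A reader might also infer that drug accounting would be out by 1.78-fold. Section 3.2 says only that a study pharmacist manages and accounts for DHAP supply; it does not tie this to the mg/kg sentence.

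**Conclusion.** The point holds as an error in the written dosing rule and should be fixed. With the tablet described, the two targets differ by a factor of 1.78 at every body weight: meeting one leaves piperaquine at 178% of its target or dihydroartemisinin at 56%. This rests on three readings of the text: the figures are targets, both amounts are on the same basis, and the combination tablet is the only source of either drug. Which component was meant to govern cannot be determined from the protocol.

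The RDT conflict between Section 2.4 and Sections 2.2.2.1 and 2.7 is also real, but lesser. The number of people it touches is not stated and is not estimated here.

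**What to change.** **Section 2.2.2.** Replace the target-dose sentence in one of two ways:
- name the governing component and its mg/kg/day dose, and give the resulting range for the other at 1:8; or
- cite the product's tablet counts by weight band.

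The sponsor or study pharmacist supplies the values from the named product. As a check, on the tablet's own basis each piperaquine limit is 8 times the matching dihydroartemisinin limit. If 18 mg/kg and 320 mg are on different salt/base bases, say so.

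**Section 2.4.** Extend the exception to the no-RDT rule to people not given DHAP for whom Section 2.2.2.1 (early or uncertain pregnancy) or Section 2.7 (refusal) calls for an RDT.

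**Section 2.2.2.1, editorial.**
- Bring the fallback for people not taking DHAP into line with the standard of care elsewhere: RDT, then AL if positive, leaving the early-pregnancy rule in place.
- In the recent-DHAP rule, change RFTAT to RFDA if that is what is meant, as it appears to be, since AL is already the drug in RFTAT.
- Exclude pregnant women in, not before, the first trimester.

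**Cost.** One dosing sentence or a short table, one clause in Section 2.4 and three small wording edits, carried into Figure 5 and the CHW materials where they differ. Sample size, power and analysis do not change.
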